**Glossary of abbreviations and terms**

| Abbreviation | Definition                                                                                               |
|---------------------|-----------------------------------------------------------------------------------------------------------------|
| ACEI                | Angiotensin Converting Enzyme Inhibitor                                                                         |
| AEFI                | Adverse Event Following Immunization                                                                            |
| AMR                 | Antimicrobial Resistance                                                                                        |
| ARNI                | Angiotensin Receptor Neprilysin Inhibitor                                                                       |
| CDC                 | Center for Disease Control and Prevention                                                                       |
| CI                  | Confidence Interval                                                                                             |
| CONSORT             | The Consolidated Standards of Reporting Trials                                                                  |
| CHF                 | Congestive Heart Failure                                                                                        |
| CRF                 | Case Report Form                                                                                                |
| DSMB                | Data and Safety Monitoring Board                                                                                |
| EDC                 | Electronic Data Capture                                                                                         |
| ERC                 | Ethic Review Committee                                                                                          |
| GWTG-HF             | Get With The Guidelines – Heart Failure                                                                         |
| HF                  | Heart Failure                                                                                                   |
| HGRAC               | Human Genetic Resources Administration of China                                                                 |
| HHRC                | Heart Health Research Center                                                                                    |
| HR                  | Hazard Ratio                                                                                                    |
| ILI                 | Influenza-like Illness                                                                                          |
| IRB                 | Institutional Review Board                                                                                      |
| NYHA                | New York Heart Association                                                                                      |
| OR                  | Odds Ratio                                                                                                      |
| PARADIGM-HF         | Prospective Comparison of ARNI with ACEI to Determine Impact on Global Mortality and Morbidity in Heart Failure |
| POV                 | Point of Vaccination                                                                                            |
| SPIRIT              | Standard Protocol Items: Recommendations for Interventional Trials                                              |
| VCR                 | Vaccine Coverage Rate                                                                                           |

## Protocol Synopsis

|                               |                                                                                                                                                                                                                                                                                                                                                                                                                                                                                                                                                                                                                                                                                                                                                                                                                                                                                                                                                                                                                                                                                                                                                                                                                                                                                                                                                                                                                                                                                      |
|-------------------------------|--------------------------------------------------------------------------------------------------------------------------------------------------------------------------------------------------------------------------------------------------------------------------------------------------------------------------------------------------------------------------------------------------------------------------------------------------------------------------------------------------------------------------------------------------------------------------------------------------------------------------------------------------------------------------------------------------------------------------------------------------------------------------------------------------------------------------------------------------------------------------------------------------------------------------------------------------------------------------------------------------------------------------------------------------------------------------------------------------------------------------------------------------------------------------------------------------------------------------------------------------------------------------------------------------------------------------------------------------------------------------------------------------------------------------------------------------------------------------------------|
| Title                  | (Population Assessment of iNfluenza and Disease Activities, PANDA II pilot)                                                                                                                                                                                                                                                                                                                                                                                                                                                                                                                                                                                                                                                                                                                                                                                                                                                                                                                                                                                                                                                                                                                                                                                                                                                                                                                                                                                                   |
| Clinical phase         | IV                                                                                                                                                                                                                                                                                                                                                                                                                                                                                                                                                                                                                                                                                                                                                                                                                                                                                                                                                                                                                                                                                                                                                                                                                                                                                                                                                                                                                                                                                   |
| Rationale              | 
Considerable data support the broad benefits of influenza vaccination in the general population. However, there is uncertainty over the effectiveness of influenza vaccination in preventing cardiovascular events in the high-risk population such as those with HF. Influenza vaccination is not covered by medical insurance in majority of China. The rate of influenza vaccination was as low as 0.6% in Chinese patients with HF, compared to about 60% in the Western European countries and in the US. Thus, it is of critical importance to detect whether providing free influenza vaccine, providing vaccination service in hospital, and educating patients as well as health provider will increase vaccine rate among patients hospitalized due to severe symptoms of HF. If so, whether improved influenza vaccine rates in patients with HF will reduced all-cause death or HF hospitalization. Before a definitive randomized cluster randomized trial, a pilot study is planned to address the following uncertainties for the design of future definitive study:
 
 
(i) Whether the intervention package is feasible;
 
(ii) Whether a target influenza vaccine rate of 90% is achievable in the intervention clusters;
 
(iii) Proportion of patients hospitalized with HF getting influenza vaccination in routine care;
 
(iv) Number of patients will be enrolled in future study.
 
 |
| Study design           | Two-arm, parallel, hospital-based, cluster randomized trial.                                                                                                                                                                                                                                                                                                                                                                                                                                                                                                                                                                                                                                                                                                                                                                                                                                                                                                                                                                                                                                                                                                                                                                                                                                                                                                                                                                                                                         |
| Intervention           | (i) education of the health care team and patients; (ii) provision of free vaccine on the day of discharge; and (iii) provision of immunization service inside hospital before discharge.                                                                                                                                                                                                                                                                                                                                                                                                                                                                                                                                                                                                                                                                                                                                                                                                                                                                                                                                                                                                                                                                                                                                                                                                                                                                                            |
| Number of participants | 330 patients; recruitment from 11 hospitals in one influenza season (average of 30 patients per hospital).                                                                                                                                                                                                                                                                                                                                                                                                                                                                                                                                                                                                                                                                                                                                                                                                                                                                                                                                                                                                                                                                                                                                                                                                                                                                                                                                                                           |
| Study duration         | 12 months                                                                                                                                                                                                                                                                                                                                                                                                                                                                                                                                                                                                                                                                                                                                                                                                                                                                                                                                                                                                                                                                                                                                                                                                                                                                                                                                                                                                                                                                            |
| Endpoints/Outcomes     | 
Primary outcomes: influenza vaccine coverage rate (VCR) in both groups.
 
Secondary outcomes: number of patients recruited during study period, rate of patient follow-up, death or readmission for HF over 3 months follow-up.
                                                                                                                                                                                                                                                                                                                                                                                                                                                                                                                                                                                                                                                                                                                                                                                                                                                                                                                                                                                                                                                                                                                                                                                                                            |

|                                    |                                                                                                                                                                                                                                                                                                                                                                                                                           |
|------------------------------------|---------------------------------------------------------------------------------------------------------------------------------------------------------------------------------------------------------------------------------------------------------------------------------------------------------------------------------------------------------------------------------------------------------------------------|
| Site inclusion criteria     | 
 
• Capable of admitting, treating, recruiting HF patients;
 
• With the capacity of treating >35 HF patients per month during recruitment period;
 
• Staff with available care team personnel to collaborate and control the lost to follow-up rate to <10%.
 
• Local approval to provide influenza vaccination from administrative bureau.
 
 |
| Site exclusion criteria     | 
 
• Participating in vaccination-related or other HF patient outcome improvement programs that might confound study outcomes.
 
                                                                                                                                                                                                                                             |
| Patient inclusion criteria  | 
 
• All adult inpatients (age ≥18 years) discharged with a diagnosis of HF during recruitment month in participating hospital;
 
• Assessed as New York Heart Association (NYHA) III-IV during hospitalization;
 
• Consent to participate in the study.
 
                                                                                                    |
| Patient exclusion criteria  | 
 
• Known allergy to influenza vaccine;
 
• Pregnant women.
 
                                                                                                                                                                                                                                                                                                        |
| Intervention administration | Staff of the participating hospitals.                                                                                                                                                                                                                                                                                                                                                                                     |
| Safety evaluation           | Adverse Event Following Immunization (AEFI) will be monitored and reported.                                                                                                                                                                                                                                                                                                                                               |
| Study schedule              | Pilot phase December 1, 2020 - November 30, 2021.
Each patient will be followed for 3 months.                                                                                                                                                                                                                                                                                                                          |
| Statistical considerations  | 
Rates of influenza vaccination (the number of patients received influenza vaccine divided by the number of patients enrolled in the intervention group and in the control group, will be reported respectively.
 
Number of patients enrolled in both the intervention and the control group will be reported.
 
Rate of patient follow-up at 3 months after enrollment will be reported.
                |
| Data Management             | A web-based electronic data capture system will be used to store and check data.                                                                                                                                                                                                                                                                                                                                          |

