Influenza vaccination is more commonly reimbursed for both the elderly and those with chronic conditions by public funding in the Americas and the Western Europe than in the Western Pacific. A government run insurance scheme for influenza vaccines seems correlates more with a higher influenza vaccine coverage rate, than with economic development status across countries. In China, the free influenza vaccine policy for people older than 60 years old is only applied in a few cities. The rate of influenza vaccination was as low as 0.6% in Chinese patients with HF, compared to about 60% in the Western European countries and in the US. Given the WHO recommendation that all people except those younger than 6 months should get influenza vaccine, the low influenza vaccine rate in China provides us a chance to study the efficacy of influenza

vaccination in reducing mortality and HF hospitalization, as neglectable low proportion of HF patients received the influenza vaccine in the routine care.

Under current vaccine regulations in China, adult immunization service can only be sought at licensed community health center or immunization clinics housed in center for disease control and prevention (CDC). Hospitals are allowed to establish a temporary Point of Vaccination (POV) after a quality check and then approval valid for three months from their local department of health. But most hospitals don't have a POV in place at the time as many of them consider vaccination being out of the scope of clinical services. Unaware of the importance of annual vaccinations, not knowing where to get vaccinated, and not wanting to pay are the top barriers prohibiting those with chronic conditions from getting influenza vaccines. Thus, it is of critical importance to investigate whether improved influenza vaccine coverage rate in patients with HF will reduced all-cause death or HF hospitalization. Before investigating the efficacy of influenza vaccines on preventing cardiovascular disease, we need to first address whether educating patients and health provider, providing vaccination service in hospital, and providing free influenza vaccine will achieve a target vaccine coverage rate (VCR) among patients hospitalized due to severe symptoms of HF.

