**Patients**

PANDA II pilot trial will focus on HF patients at higher risk of having serious complications from influenza infection. HF is largely a clinical diagnosis. Based on the widely used Boston criteria, HF will be defined according to the attending physician's report of any of the following clinical symptoms described as dyspnea ('unusual' on light exertion or recurrent in the supine position); fluid retention; description of 'rales' in the lungs, jugular venous distension, or pulmonary edema on physical examination; or pulmonary edema on chest x-ray presumed related to cardiac dysfunction. HF patients will be identified through screening the admission list of a cardiovascular ward in each participating hospital for the following eligibility criteria.

Inclusion criteria for participating patients:

- 1) all the adult inpatients (age  $\geq 18$  years) with a discharge diagnosis of HF during recruitment month in participating hospitals;
- 2) assessed as New York Heart Association (NYHA) function classification III-IV during hospitalization;
- 3) consent to participate in the study.

Exclusion criteria for participating patients:

- 1) have known allergy to influenza vaccine.
- 2) pregnant women.

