### **Outcomes**

#### *Primary outcome*

- Rate of uptake of influenza vaccination among eligible patients in the intervention hospitals and that in the control hospitals;
- Number of patient recruited;
- Rate of adherence to follow-up;

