### **Participant timeline**

This pilot study will be conducted between December 2020 and November 2021. Participating centers and participants will be recruited in December 2020. Both hospitals and patients will go through their eligibility screening respectively. Eligible hospitals and patients will then be informed about the study, potential benefits and risks, and be asked for consent. Consented hospitals will be randomized into intervention or control arm before the commencement of the study. Eligible patients will be assessed through collecting their baseline demographics, disease history, and clinical characteristics during hospitalization. On the day of discharge, eligible patients in intervention hospitals will receive influenza vaccine shots. Face-to-face follow-up visits for each patient will be scheduled at 1-month and 3-month post discharge. Study outcome data will be collected during the follow-up visits. If the patient is unable to return for such a visit, they will receive a telephone call instead.

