### **Recruitment**

An estimated average of 30 patients per hospital will be set for recruitment. The admission list from each participating site will be monitored to ensure recruiting consecutive heart failure patients to prevent potential selection bias. If a quota of 50 patients is reached in any given hospital, the recruitment process will end.

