### **Data collection methods**

Case report forms (CRFs) at screening, baseline, admission, intervention, vaccination, discharge, 1-month and 3-month follow-up will be designed to collect patient characteristics and study outcomes. Data will be assessed by site investigator team and sampled by steering committee. Outcome data will also be collected for patients who drop out of or drop in to the intervention.

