| TIMEPOINT                                                                 | November                                  | December   | January         | February | March | April     |
| ENROLMENT:                                                         |                                           |            |                 |          |       |           |
| Hospital and patients eligibility screen                                  | X                                         |            |                 |          |       |           |
| Hospital and patients informed consent                                    | X                                         |            |                 |          |       |           |
| Allocation                                                                |                                           | X          |                 |          |       |           |
| INTERVENTIONS:                                                     |                                           |            |                 |          |       |           |
| [Intervention arm (education + vaccination)]                       |                                           | X          |                 |          |       |           |
| [Control arm (usual care)]                                         |                                           | X          |                 |          |       |           |
| ASSESSMENTS:                                                       |                                           |            |                 |          |       |           |
| [baseline demographics, clinical characteristics, and vaccination] | X                                         | X          |                 |          |       |           |
| [recruitment rate]                                                 | X                                         | X          |                 |          |       |           |
| [vaccination logistics, immunization service license]              |                                           |            | X               | X        |       |           |
| [adherence rate]                                                   |                                           |            |                 | X        | X     |           |

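### Vaccine coverage is fixed over enrolled, consenting patients, so 90% among them need not mean 90% of hospitalized heart failure patients, and the word *eligible* blurs the denominator

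*Protocol*

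**What the plan says.** - **Formula.** Protocol Synopsis, Statistical considerations, sets the vaccination rate as "the number of patients received influenza vaccine divided by the number of patients enrolled in the intervention group and in the control group".
- **Primary outcome.** The Outcomes section words it as "Rate of uptake of influenza vaccination among eligible patients in the intervention hospitals and that in the control hospitals".
- **Consent.** The third patient inclusion criterion is "consent to participate in the study". On that list, *eligible* and *enrolled* are the same patients. The Participant timeline uses the word for an earlier stage: "Eligible hospitals and patients will then be informed about the study, potential benefits and risks, and be asked for consent".
- **Question.** The Background wants to know whether the package "will achieve a target vaccine coverage rate (VCR) among patients hospitalized due to severe symptoms of HF". The Background and the Synopsis rationale also ask whether 90% can be reached in the intervention clusters. Neither statement is limited to consenting patients.
- **Delivery.** The Randomization section says that every eligible patient at an intervention hospital is to be vaccinated. The Blinding section says the trial is open label.
- **Data on hand.** The Recruitment section has the admission list monitored so that consecutive patients are recruited, and it closes a site at a quota: "If a quota of 50 patients is reached in any given hospital, the recruitment process will end". The Data collection methods section lists a screening form and adds: "Outcome data will also be collected for patients who drop out of or drop in to the intervention". Figure 1 lists a recruitment rate without defining its denominator.

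**The concern.** A patient who declines the study leaves both the numerator and the denominator of the enrolled VCR. All eligible patients at intervention hospitals are to be vaccinated and the trial is open label, so willingness to join and willingness to be vaccinated may overlap. If they do, those least likely to accept vaccine are the ones the rate cannot see.

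At stake is the pilot's answer on the 90% target. Under the plan as written, 90% could be reported as achievable in the intervention clusters when it was shown only in patients who agreed to take part. The loose use of *eligible* adds to this, because a reader of the Outcomes section could take the reported rate to cover patients approached before consent.

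The point concerns only patients who never enrol. Enrolled patients who drop out of the intervention stay under observation and count correctly as unvaccinated.

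**Working it through.** **Planned size.** 11 hospitals x 30 patients = 330, which reproduces the Synopsis figure. The 7:4 allocation gives 7 x 30 = 210 intervention and 4 x 30 = 120 control patients. The sample size is a practical number, so there is no power calculation to reproduce.

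**Inputs.**
- V, the VCR among enrolled patients: set at the 90% target (Background), that is 189 of 210.
- c, the share of otherwise eligible patients who consent: not in the protocol; assumed 95%, 90% or 80%.
- a, vaccine uptake among those who decline: not in the protocol; assumed 0%, 0.6% (the routine-care figure in the Background), 50% or 90%.

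**Formula.** VCR over the pre-consent group = c x V + (1 - c) x a. The excess of the enrolled VCR over it is (1 - c) x (V - a). This is positive if decliners accept less often, zero if c = 1 or a = V, and negative if they accept more often.

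**Intervention arm, V = 90%.**

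| Uptake in decliners (a) | c = 95% | c = 90% | c = 80% |
|---|---|---|---|
| 0% | 85.5% | 81.0% | 72.0% |
| 0.6% | 85.5% | 81.1% | 72.1% |
| 50% | 88.0% | 86.0% | 82.0% |
| 90% | 90.0% | 90.0% | 90.0% |

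Example: 0.90 x 0.90 + 0.10 x 0 = 0.810, an excess of 9 percentage points.

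**Room for decliners.** If decliners are counted as unvaccinated, the rate is vaccinated / (210 + n), where n is the number of decliners across the seven intervention hospitals. The largest n that keeps it at 90% or more is:
- 189 vaccinated: n = 0 (189/211 = 89.6%).
- 200 vaccinated: n = 12 (200/222 = 90.1%; 200/223 = 89.7%).
- 210 vaccinated: n = 23 (210/233 = 90.1%; 210/234 = 89.7%).

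**Limit of that rate.** With a = 0 it equals c x V, which is at most c. Below 90% consent it cannot reach 90% even if every enrolled patient is vaccinated.

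**Control arm, V = 0.6%, a = 0.** The result is 0.57%, 0.54% and 0.48% at the three consent rates, a difference of at most 0.12 points. The issue matters only in the intervention arm.

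**Where the pre-consent group must stop.** Take an assumed site that enrols 50, vaccinates 45 and has 5 refusals: 45/55 = 81.8%. Adding 5 patients discharged after the quota closed the site, and never approached, would give 45/60 = 75.0% with no further refusal. The group should therefore include only patients screened before closure.

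**The case against.** The strongest defence is that the pilot exists to plan a definitive trial. If that trial also takes individual consent, vaccinated over enrolled is the exposure figure it needs. The Background sentence can be read as a prose description of the population that the inclusion criteria then define, and such a sentence would not normally mention consent. The formula in the Synopsis is explicit. The recruitment rate in Figure 1, the admission list and the screening form show that data on non-enrolment are partly foreseen. The size of the gap is wholly assumed.

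Most of this stands. The enrolled VCR is a valid primary measure, and no overstatement is demonstrated. What remains is that it is the only coverage rate the protocol fixes, while the 90% question is put to hospitalized patients and intervention clusters. Figure 1's undefined recruitment rate does not fill that gap, and the Outcomes section lists only the number recruited.

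A reader might infer three stronger points that the protocol does not support:
- **A flat contradiction between the Synopsis and the Outcomes section.** With consent on the inclusion list, the two can agree. The doubt comes from the other use of the word in the Participant timeline.
- **Selective enrolment by arm.** Figure 1 places "Hospital and patients informed consent" in November and allocation in December, while the Participant timeline has hospitals randomized before the study starts. Whether patients know the allocation when they consent is uncertain, and the point here does not need it.
- **A 90% pass mark on the pre-consent rate.** That would turn a vaccine-uptake target into a research-consent target. Patients may decline because of data collection or follow-up visits and still accept vaccine.

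**Conclusion.** The point holds in a limited form. The denominator is ambiguous between two sections. The enrolled VCR overstates coverage of hospitalized NYHA III-IV patients only on condition that those who decline the study accept vaccine less often. Over the assumed consent range of 95% to 80%, with 90% among enrolled patients, the overstatement is 4.5 to 18 points if no decliner is vaccinated and nil if decliners accept equally often. The protocol supplies neither consent rate nor decliner uptake, so these figures illustrate and do not estimate. The control arm is practically unaffected. The primary measure need not change. The correction is worth making because the 90% conclusion could otherwise be stated for a wider group than was observed.

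**What to change.** 1. In the Primary outcome section, replace *eligible* by *enrolled*, so that it matches the Synopsis formula.
2. From the admission list and screening form, report by arm: the number of patients who meet inclusion criteria 1 and 2, have no exclusion and were screened before the site closed recruitment (including closure at the quota of 50); the consent rate; and how many declined because of the vaccine.
3. Beside the primary VCR, report a supplementary VCR over that pre-consent group, with non-consenters counted as unvaccinated. Label it a lower bound and give it a confidence interval that allows for clustering, as the Analysis section already intends for individual-level data.
4. Word the 90% conclusion as applying to consenting patients unless the lower bound also supports it. Do not use the lower bound as a pass/fail test.

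The cost is a wording change and one count, with reason, on an existing form. No patients or visits are added. The downside is a second, less favourable figure, which is pessimistic if some non-consenters would have accepted vaccine. Anonymous counts of non-consenters may also need the ethics committee's agreement.
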